### Statistical analysis plan

#### Sample size

The sample size for FEDORA is 30 patients. For the fedratinib plus ropeginterferon alfa-2b combination treatment to be considered acceptable, 80% of patients would need to tolerate treatment. If 60% or fewer patients tolerated treatment, then the combination would be considered unacceptable. Based on this, if there is a high probability that the true tolerability rate is greater than 70% then the treatment would warrant further investigation. Employing a conjugate beta-binomial analysis, with a minimally informative Beta(1,1) prior, if 23 of the 30 patients tolerate the treatment combination we would be 76% sure that the true tolerability is greater than 70%, and therefore warrant further investigation (Appendix 7).

#### Interim and final analysis

No formal interim or pre-defined sub-group analyses are planned. Accumulating data and analyses will be monitored regularly by the TSC on a nine-monthly basis, or more frequently if required to monitor safety, recruitment, data quality, and activity. Final analysis of all outcome measures will be performed after all patients have completed a minimum of two years follow-up.

All analysis will be modified intention to treat (mITT) unless otherwise specified, with all patients who are recruited into the trial that receive at least one cycle of combination therapy included, irrespective of trial deviations and discontinuations. Patients who commence pre-treatment with fedratinib, but who do not then go on to receive concurrent ropeginterferon alfa-2b for any reason, or those who withdraw from the trial before the four-month primary outcome time-point for reasons unrelated to treatment toxicity or tolerability will be deemed unevaluable and replaced, and not included in the mITT analysis. Sensitivity analysis of outcomes will consider patient compliance with the treatment schedule and patients who do not receive at least one cycle of combination treatment.

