#### Outcome analysis

For the primary outcome, the total number and proportion of patients tolerating four months of treatment will be reported alongside the associated 95% credible interval, using the total number of patients who started combination therapy as the denominator (including patients who failed to find any tolerable dose). Bayesian posterior probability plots will be presented alongside the probability that the true tolerability rate is greater than 70%.

Analyses of the secondary and exploratory outcomes will be descriptive in nature, with no hypothesis testing conducted.The total number and proportion of patients tolerating up to two years of combination therapy will be reported alongside the associated 95% credible interval, using the total number of patients who started combination therapy as the denominator.Best overall response rate will be presented as the number and proportion of patients achieving a response, overall and by response category, over the total number of patients receiving combination treatment.The number and proportion of patients will be reported against the highest tolerated ropeginterferon alfa-2b dose that each individual patient received, having followed dose escalation schedule.Toxicity will be presented as the number and proportion of patients experiencing one or more grade ≥ 3 AEs, or a SAE of any grade. This outcome will be analysed using the safety population.Overall and progression-free survival will be presented using Kaplan–Meier plots. The median time to event and survival estimates at one year will be presented with 95% confidence intervals where appropriate.The MFSAF v4.0 analyses will be presented as medians with interquartile ranges over time. Multi-level models may be used to compare changes in scores from baseline to 12 months if appropriate.Bone marrow fibrosis will be tabulated and presented graphically, with number and proportion of patients at each level reported. In addition to this, individual patient results will be plotted to show change over time at the patient level.The *JAK2*^V617F^ mutant allele frequency will be presented as medians and interquartile ranges over time, overall and split by highest dose of ropeginterferon alfa-2b tolerated and summarised using descriptive statistics. Individual patient plots will also be presented showing raw percentages.

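### The protocol gives two different populations for the primary tolerability analysis, and they differ in patients who fail from toxicity in cycle 1

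*Protocol article*

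**What the plan says.** The Interim and final analysis section of the protocol article makes mITT the set for all analyses unless the plan says otherwise. It defines that set as "all patients who are recruited into the trial that receive at least one cycle of combination therapy included, irrespective of trial deviations and discontinuations". It lists two groups as unevaluable and replaced: patients who never go on to ropeginterferon alfa-2b, and patients who withdraw before the four-month time-point for reasons unrelated to toxicity or tolerability. It then adds: "Sensitivity analysis of outcomes will consider patient compliance with the treatment schedule and patients who do not receive at least one cycle of combination treatment".

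The Outcome analysis section reports the primary outcome "using the total number of patients who started combination therapy as the denominator (including patients who failed to find any tolerable dose").

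Under Trial outcomes, a patient counts as not tolerating if drug-related toxicity leads to discontinuation of either drug, to a delay of more than 28 consecutive days, or to death, within four months of starting the combination. Cycles last 28 days, so cycle 1 lies inside that window.

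**The concern.** The two population statements do not describe the same patients. A toxicity discontinuation or toxic death during cycle 1 is a failure under Trial outcomes and belongs to the started-therapy denominator. If receiving at least one cycle means a full cycle, the same patient is outside the mITT set. Entry to that set would then depend on part of the outcome being measured, and every toxicity patient it leaves out would be a failure.

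This is the only primary outcome of a 30-patient, single-arm, open-label trial whose result informs the phase III decision. Two analysts following different sentences could report different posterior probabilities from the same data, and the denominator could be settled after the data are known.

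**Working it through.** **Inputs** (Sample size section)
- "The sample size for FEDORA is 30 patients".
- Acceptable: "80% of patients would need to tolerate treatment". Unacceptable: "If 60% or fewer patients tolerated treatment, then the combination would be considered unacceptable".
- Decision quantity: "if there is a high probability that the true tolerability rate is greater than 70% then the treatment would warrant further investigation".
- Analysis: conjugate beta-binomial "with a minimally informative Beta(1,1) prior". The worked example is 23 of 30, giving 76%.

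**Assumptions not in the documents**
- The go level is the posterior reached by 23 of 30. The article gives no other numerical meaning for a high probability.
- A share f of all failures occurs before cycle 1 is complete, with f = 10%, 25% or 50%.

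**Step 1: the plan's own figure.** With x tolerating out of n, the posterior is Beta(1 + x, 1 + n − x). For 23 of 30 this is Beta(24, 8), and P(rate > 0.70) = 0.755. The stated 76% is reproduced.

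**Step 2: the same patients under the two definitions.**

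| Tolerating | All starters | P(> 70%) | Cycle-1 failures dropped | Set left | P(> 70%) |
|---|---|---|---|---|---|
| 22 | 30 | 61.4% | 2 | 28 | 81.2% |
| 21 | 30 | 45.8% | 3 | 27 | 78.0% |

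Both results lie below the 75.5% level on all starters and above it once the cycle-1 failures are dropped.

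**Step 3: chance of a go.** With all 30 starters counted, P(go) = P(X ≥ 23), X ~ Bin(30, p). This is 4.4% at p = 0.60, 28.1% at 0.70 and 76.1% at 0.80.

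If cycle-1 failures are removed, the apparent rate is q = p / (1 − f(1 − p)). At p = 0.60:
- f = 10%: 0.60 / 0.96 = 0.625
- f = 25%: 0.60 / 0.90 = 0.667
- f = 50%: 0.60 / 0.80 = 0.750

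Two cases follow:
- *Without replacement:* 30 start and K ~ Bin(30, f(1 − p)) are dropped. Among the 30 − K left, the number tolerating is Bin(30 − K, q). The result is a go if the posterior reaches the 23-of-30 level.
- *Still 30 analysed:* P(X ≥ 23), X ~ Bin(30, q).

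| True rate | All starters | No replacement, f = 10 / 25 / 50% | 30 analysed, f = 10 / 25 / 50% |
|---|---|---|---|
| 60% | 4.4% | 5.8 / 12.4 / 39.9% | 7.6 / 16.7 / 51.4% |
| 70% | 28.1% | 31.8 / 45.5 / 75.0% | 37.5 / 54.9 / 85.4% |
| 80% | 76.1% | 78.5 / 86.1 / 96.2% | 82.8 / 91.1 / 98.6% |

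**Step 4: a second mismatch.** A patient who starts the combination and then withdraws before four months for a non-toxicity reason is excluded and replaced under Interim and final analysis. The same patient is a starter under Outcome analysis. The two sections cannot both be followed literally for this patient either.

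**The case against.** A reader might infer that cycle-1 toxicity failures do drop out of the primary analysis and that the go probability is therefore inflated. The documents do not support that as a statement of fact, for four reasons.

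- The mITT default gives way where the plan specifies something else, and Outcome analysis specifies a denominator for this very outcome. Its parenthesis explicitly keeps patients who found no tolerable dose. If the specific statement overrides the general one, nobody is lost and nothing is inflated.
- The mITT wording does not say that the cycle must be complete, whereas the definition of the highest tolerated dose under Trial outcomes does. The list of unevaluable patients leaves out toxicity withdrawals, which suggests that they stay in.
- Cycle-1 toxicity failures are not listed among replaced patients, so the figures with 30 still analysed rest on a replacement that the article does not state.
- A share of 50% in cycle 1 is extreme for this design. A tolerable fedratinib dose is established first, cycle 1 uses the lowest scheduled ropeginterferon dose, and the Discussion expects little toxicity at that level.

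All four points stand, and they make the bias conditional. They do not remove the inconsistency. A sensitivity analysis that considers patients with less than one cycle makes sense only if the main analysis omits them. The mITT exclusions are written around the primary-outcome time-point, so they were meant to reach this outcome. Where Outcome analysis moves an outcome to another set, it names the set (the safety population, for toxicity), and it names none for tolerability. The override is a reasonable reading, but the text does not settle it.

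**Conclusion.** The point holds as an inconsistency to be reconciled, with bias only under one of the two readings. If the started-therapy denominator governs, there is no bias. If the mITT text is applied and a full cycle is required, the toxicity patients removed are all failures, and the error can only favour a go.

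Two such patients are enough to carry a result across the 23-of-30 level. At the unacceptable 60% rate, the chance of a go rises from 4.4% to between 5.8% and 40% without replacement. The range is 7.6% to 51% if 30 are still analysed. The direction does not depend on the assumptions. The size does: it rests on an assumed 10% to 50% of failures in cycle 1, with the top of that range unlikely, and on reading the 23-of-30 example as the go level.

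**What to change.** In Interim and final analysis, state that:

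1. the primary tolerability set is every patient who receives at least one dose of ropeginterferon alfa-2b with fedratinib;
2. toxicity failures from that first dose onward count as not tolerating and are not replaced;
3. the one-cycle set is used for this outcome only as a sensitivity analysis, with the existing sensitivity sentence reworded to match.

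Also reconcile the exclusion and replacement of non-toxicity withdrawals with the denominator in Outcome analysis. One way is to state the exclusion there as well and report a sensitivity analysis on all starters.

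The cost is wording in the protocol and in any analysis plan that repeats it. No new data are needed. The reported tolerability may be slightly less favourable than under the one-cycle set.

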#### Fedratinib

During the pre-treatment stage, a tolerable dose of fedratinib must be established for 28 days (one cycle) before ropeginterferon alfa-2b can be started. Two dose reductions are permitted; to 300mg daily and then to 200 mg daily. Patients who require more than two dose reductions during fedratinib monotherapy should not continue to combination therapy and should be withdrawn from the trial.

The dose modifications for haematological and non-haematological toxicities, and treatment of emergent toxicities and management of Wernicke’s encephalopathy are shown in the Appendix 5. If the adverse reaction that results in a dose reduction is controlled, and the toxicity is resolved for at least 28 days, then the dose level may be re-escalated to one dose level higher per month up to the original dose level. Dose re-escalation is not recommended if the dose reduction was due to a grade 4 non-haematological toxicity, grade 3–4 alanine transferase, aspartate aminotransferase, or total bilirubin elevation, or re-occurrence of a grade 4 haematological toxicity.

Fedratinib should be reduced to 200mg once daily if concomitant treatment with strong CYP3A4 inhibitors cannot be avoided and patients carefully monitored. If the strong CYP3A4 inhibitor is discontinued, fedratinib should be increased to 300mg once daily during the first two weeks, and then 400mg once daily thereafter as tolerated.

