### Trial outcomes

The primary outcome is tolerability of combination therapy. A patient is classified as not tolerating treatment if they discontinue either fedratinib or ropeginterferon alfa-2b due to drug-related toxicity, due to delays in treatment exceeding 28 consecutive days due to drug-related toxicity, or if a treatment toxicity-related death is reported, within four months of starting combination therapy.

The secondary outcomes are:Tolerability of combination therapy throughout the treatment course. A patient is classified as not tolerating treatment as per the definition for the primary outcome.Best overall response (complete plus partial response) assessed using International Working Group criteria (spleen size measure by palpation) [30] within 12 and 24 months from starting combination treatment. Patients who die or do not have a disease response recorded prior to the relevant time points will be classified as non-responders.The highest tolerated dose of ropeginterferon alfa-2b, in combination with fedratinib, achieved by each patient. To be tolerated, the dose must have been maintained for at least one complete cycle.Toxicity, defined to be any grade ≥ 3 AE, or a SAE of any grade. See the Adverse Events Reporting and Analysis section for details.Overall survival, defined as the time from starting combination therapy to date of death from any cause. Patients who are alive at the time of analysis or lost to follow-up will be censored at their date last seen.Progression-free survival, defined as the time from starting combination therapy to first event or death from any cause. An event is defined to be any of the following: an increase in bone marrow fibrosis, an increase in spleen size by > 5cm, or transformation to acute myeloid leukaemia. Patients who are alive and event-free at the time of analysis or lost to follow-up will be censored at their date last seen.Quality of life assessed using the myelofibrosis symptom assessment form (MFSAF) v4.0 [31] total symptom score at trial entry, and three-monthly during treatment.Bone marrow fibrosis, assessed using consensus definitions [32] at trial entry and six-monthly during treatment.

The *JAK2*^V617F^ clone size, measured at trial entry and three-monthly during treatment, is an exploratory outcome.

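### The rule that drops and replaces early non-toxicity withdrawals is written for the four-month tolerability outcome but also governs PFS and OS, and it contradicts the stated denominators for response and tolerability

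*Protocol article*

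**What the plan says.** The Interim and final analysis section sets the default: "All analysis will be modified intention to treat (mITT) unless otherwise specified". The inclusion sentence is broad: patients who "receive at least one cycle of combination therapy included, irrespective of trial deviations and discontinuations". The next sentence narrows it. Patients who never go on to ropeginterferon are excluded, and those who withdraw from the trial before the four-month time-point "for reasons unrelated to treatment toxicity or tolerability will be deemed unevaluable and replaced, and not included in the mITT analysis". On sensitivity analyses the section says: "Sensitivity analysis of outcomes will consider patient compliance with the treatment schedule and patients who do not receive at least one cycle of combination treatment".

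Other sections bear on the same patients:

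- **Trial outcomes.** The PFS definition reads "Progression-free survival, defined as the time from starting combination therapy to first event or death from any cause". OS has the same starting point. Both censor patients lost to follow-up at the date last seen. For best response, a patient who dies or has no response on record counts as a non-responder.
- **Outcome analysis.** Response is presented "over the total number of patients receiving combination treatment". Tolerability at four months and up to two years is divided by everyone who started combination therapy. Toxicity uses the safety population. PFS and OS have no population or denominator of their own.
- **Dose modifications, delays, and discontinuations.** Confirmed progression is listed as a reason to stop trial treatment.
- **Table 2.** Survival and progression are still collected every three months after treatment ends.

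**The concern.** Calling an early non-toxicity leaver unevaluable makes sense for an outcome that asks whether a patient tolerated four months of treatment. It makes no sense for PFS or OS. Their clock starts with combination therapy, so months 0 to 4 are time at risk, and the censoring rule already deals with patients who leave. Removing them selects the analysis set on what happened after time zero.

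Replacement does not repair this. The new recruit is subject to the same rule, so the final 30 are by construction patients who did not leave early for a non-toxicity reason. If some who left did so because their disease was worsening, reported PFS is too favourable. The reason for leaving is also judged open-label.

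The Choice of trial design section names best overall response and PFS as the place where evidence of activity will be sought, and the trial is meant to inform a phase III decision. With 30 patients, two or three removals are visible in the estimate.

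**Working it through.** **1. The plan's own figure.** The Sample size section gives 76% probability that true tolerability exceeds 70% if 23 of 30 tolerate, with a Beta(1,1) prior. The posterior is Beta(1+23, 1+7) = Beta(24, 8), and P(p > 0.70) = 0.755. The figure reproduces and is not in dispute.

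**2. Which outcomes the exclusion reaches.**

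| Outcome | Own population or denominator? | Effect of the exclusion |
|---|---|---|
| PFS | None | Applies by default |
| OS | None | Applies by default |
| Best response | All receiving combination treatment, plus a non-responder rule | Contradiction |
| Tolerability, four months and two years | All who started combination therapy | Contradiction |
| Toxicity | Safety population | Not affected |

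The listed sensitivity analyses cover compliance and patients with less than one combination cycle. Neither names a patient who completed a cycle and then withdrew before month four.

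**3. Size for PFS.** The article gives neither an expected PFS nor a count of early withdrawals, so both are assumptions. Let k patients progress, withdraw before month four and be removed. Let N = 30 + k be the number who started, and e = 0.25 the true proportion with an event by one year (one-year PFS 75%), with no censoring. Event counts are expected values and need not be whole numbers.

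Reported one-year PFS = 1 − (N·e − k)/(N − k)

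| k | N | Expected events, all starters | Events left after removal | Reported PFS |
|---|---|---|---|---|
| 0 | 30 | 7.5 | 7.5 | 1 − 7.5/30 = 75% |
| 2 | 32 | 8 | 6 | 1 − 6/30 = 80% |
| 3 | 33 | 8.25 | 5.25 | 1 − 5.25/30 = 82.5% |
| 4 | 34 | 8.5 | 4.5 | 1 − 4.5/30 = 85% |

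This is the true value multiplied by (30 + k)/30.

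**4. Size of the contradiction for response.** With 10 responders and k = 3, the denominator under Outcome analysis gives 10/33 = 30.3%, and the mITT exclusion gives 10/30 = 33.3%. Two analysts could each follow the text and report different rates.

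**5. Size of the contradiction for the primary outcome.** Take 23 tolerating among 30 evaluable patients, and suppose k replaced patients are kept because the stated denominator is all starters. Counted as not tolerating, the posterior is Beta(24, 8 + k), and P(p > 0.70) is 0.66, 0.55 and 0.45 for k = 1, 2 and 3. Counted as tolerating, it is Beta(24 + k, 8), and the probability is 0.79, 0.82 and 0.84. These are bounds, not corrections. They show only that the denominator has to be settled.

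**The case against.** The strongest reply is that the rule covers patients who withdraw from the trial, not those who stop treatment. Progression is listed as a reason to discontinue treatment, discontinuations are kept in the mITT set, and follow-up for progression and survival continues afterwards. On that reading a patient who stops at progression in month two stays in the analysis. A reader might instead infer that every early progressor is deleted, because the Fedratinib section says that patients needing more than two dose reductions on monotherapy "should not continue to combination therapy and should be withdrawn from the trial". The documents do not support that inference. The sentence concerns patients who never start the combination, and does not show that stopping combination treatment amounts to leaving the trial. What remains is that the article does not define withdrawal, and that even on the narrow reading a patient who progresses and then withdraws is removed.

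A reader might also infer that the exclusion distorts every mITT outcome. That goes too far, for four reasons:

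- The mITT default yields where something else is specified. On a plain reading, the response and tolerability denominators override it, which leaves a conflict of wording rather than a clear deletion.
- A patient lost after withdrawal would be censored for OS in any case, so OS bias needs a known death to be discarded.
- The first scheduled post-baseline marrow is at month 6, so little fibrosis information is lost by month four. Scheduled detection of early progression then rests on palpation and blood blasts, which narrows the PFS route too.
- Patients who leave event-free would be censored, so removing them changes PFS little or not at all.

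The PFS scenarios are also demanding. They put 2/8 = 25%, 3/8.25 = 36% or 4/8.5 = 47% of first-year events before month four, all in patients who then withdraw. Finally, the only stated criterion for going forward is tolerability above 70%. Activity outcomes are descriptive and carry no threshold.

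**Conclusion.** The point holds in a limited form. As written, a rule designed for the four-month tolerability outcome also governs PFS and OS. It can remove a recorded early progression from PFS, and no listed sensitivity analysis is named for these patients. For response and both tolerability outcomes the defect is a contradiction between two sections, not a demonstrated deletion.

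Any bias in PFS would be optimistic, but its size depends on a count the article does not give. It is nil if nobody progresses and withdraws before month four. Under the assumed 75% one-year PFS without censoring, it is 5, 7.5 or 10 percentage points for 2, 3 or 4 such patients. The tolerability decision figure of 76% stands as calculated. The change is worth making because PFS is one of the two named sources of evidence on activity and the remedy is simple.

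**What to change.** 1. Limit the unevaluable-and-replace rule to the four-month primary outcome.
2. Analyse PFS, OS, best response and two-year tolerability in all patients who started combination therapy. For PFS and OS, count progressions and deaths known before or after withdrawal as events, and censor the rest at the date last seen. For response, count patients with none recorded as non-responders.
3. Define withdrawal from the trial, and state that stopping treatment at progression is not withdrawal.
4. Reconcile the exclusion with the denominators under Outcome analysis, including the one for the primary outcome. Counting replaced patients as not tolerating could be added as a worst-case bound, but this is optional.

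The cost is protocol and SAP wording. Post-treatment follow-up for survival and progression is already scheduled, so no new data collection is needed. The downside is that activity estimates may be slightly less favourable.
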